#### Sham exercise (EX-S)

The EX-S does not put strain on the cardiovascular system, so as to avoid a potential aerobic effect, and avoids incorporating progressive resistance strengthening (the use of weights are not permitted) as improvement in aerobic capacity [23] and lower limb muscle strength [24] have been associated with faster cognitive processing speed. Moreover, no focused dual task activities are performed during the training sessions, so as to avoid any potential cognitive training. Hence the EX-S is focusing on balance, co-ordination and stretching, which is a credible sham exercise comparator.

The EX-S sessions have been designed to reflect the EX intervention for time and attention, hence the frequency and duration of sessions, and the manner in which the training times progress throughout the 12 week program mimic that described above. During all EX-S sessions at least one exercise from each of six different categories is performed to allow variation; these are selected on the basis of individual need (exercises summarized in Table 4). To ensure that exercises are at a light intensity, heart rate and rate of perceived exertion (RPE) are monitored throughout the training sessions, after completion of each exercise (i.e. a minimum of six times). Should either the HR or RPE increase above pre-set criteria, an enforced rest is required by the participant to prevent any potential aerobic effect of the exercise. The EX-S protocol builds on a sham intervention that was applied in a previous study in people with MS [25].

**Table 4 Tab4:** Exercise categories of the sham treatment and the subsequent exercise selection of each category

**Type 1:** **Stretches**	**Type 2:** **Exercises in crook lying**	**Type 3:** **Exercises in side lying**
a) Hamstrings b) Quadriceps c) Hip Flexors d) Hip Abductors e) Bilateral hip abductor f) Ankle plantar-flexors	a) Bridging (two legs/single leg) b) Trunk rotation c) Pelvic tilt d) Unilateral hip abduction/ bilateral hip abduction e) Hip and knee flexion/extension	a) unilateral hip abduction b) unilateral hip abduction/ lateral rotation c) Unilateral knee flexion/extension
**Type 4:** **Exercises in prone**	**Type 5:** **Exercises in unsupported sitting**	**Type 6:** **Exercises in standing**
a) Unilateral hip extension b) Unilateral/bilateral knee flexion c) Bilateral isometric gluteal contractions d) Unilateral/bilateral hip rotation	a) Anterior/posterior pelvic tilt b) Trunk rotation c) Forward trunk flexion d) Unilateral trunk extension (reach out of base of support) e) Unilateral knee extension/flexion f) Unilateral hip abduction g) Bilateral hip abduction	a) Squats (two legs/single leg) b) Step-ups onto low step c) Balancing on one leg (single-leg stance) d) Sideways stepping e) Backwards stepping f) Balancing in step-stance g) Lateral reaching out of base of support

[25]

#### Follow up

To encourage people to continue exercising post supervision the goals of the person with MS will be discussed and taken into account at the beginning of the program, and then reviewed on a further three occasions (every 4 weeks) during the 12 week intervention. This is a practical, and commonly used strategy for positively affecting behavioral change and engagement with rehabilitation programs [26].

### Study status

By March 2020, a total of 135 participants have been randomized into the study. Of these, 40 are now in the intervention phase, 90 have completed the immediate follow up, 63 have completed the 3-month follow up and 37 have completed the 6-month follow up.

### Outcomes and assessments

#### Primary outcome

The primary outcome of this study is the change in processing speed (PS) over the 12 weeks of training, assessed with the Symbol Digit Modalities Test (SDMT). The SDMT is available in several versions, and in the present study, 3 versions will be used in a randomized order to minimize practice effects when repeated [27]. There are several reasons why we chose PS as the primary outcome measure. First, it is well known that PS is the primary cognitive impairment in persons with MS [28] and as a primary cognitive construct, impaired PS itself can lead to problems in higher cognitive functioning such as executive abilities [29]. As such, improving PS may also improve other cognitive areas. Second, there is good preliminary data from smaller studies from multiple laboratories that both CR and exercise improve PS [24, 30–32]. Third, the existing RehaCom literature shows the most consistent and significant effect on PS [18, 33–36]. Fourth, a recent topical review of the SDMT found strong evidence supporting the reliability and validity of the test and recommended a responder definition of SDMT change approximating 4 points or 10% in magnitude [37]. Lastly, after an extensive review of potential cognitive outcome measures by the Multiple Sclerosis Outcome Assessment Consortium, the SDMT was recommended to the Federal regulators as *the* cognitive test of choice to be included in MS clinical trials [38].

#### Secondary outcome

All secondary outcomes will be assessed during the in-person interview or the baseline assessment, at the post 12-week assessment and at the 24-week follow-up assessment.

#### Study assessments

Study assessments are composed of the neuropsychological and exercise assessments, MRI, and the completion of the patient reported outcomes (PROs).

For a detailed overview of all outcomes and the timing of assessment see Table 5.

**Table 5 Tab5:** Overview of assessments at different test-sessions

**Outcome**	**Initial Screening**	**In person Screening**	**Baseline Assessment**	**12-week intervention**	**Immediate Post 12-week Assessment**	**3-months follow-up Interview**	**6-months follow-up Assessment**
**Cognitive**							
BICAMS*							
**SDMT**		**X**			**X**		**X**
Token Test		X					
BICAMS*							
CVLT			X		X		X
BICAMS*							
BVMT-R			X		X		X
WTAR or NART			X				
**Physical**							
Visual Acuity test		X					
ActiGraph Device		X		X**			
CMI			X		X		X
6MWT			X		X		X
IET			X		X		X
Functional MRI***			X		X		X
**PRO´s**							
Fitness Questionnaire****	X						
GLTEQ	X						
Demographic form		X					
BDI-II		X					
FAMS			X		X		X
EQ-5D-5L			X		X		X
MSIS-29-V2			X		X		X
MSWS-12			X		X		X
PDQ-20			X		X		X
MFIS			X		X		X
HADS			X		X		X
**Customized**							
Phone Interview	X						
Consent form		X					
Medication list		X			X		X
Goal Setting Sheet				X			
Adverse Event form*****				X			
Post Intervention Interview						X	
Post Intervention Survey							X
Serious Adverse Event form*****							X

*Available in three parallel versions;** measured during the week following the intervention; ***only performed at 3 sites; **** AHA/ACSM Health/Fitness Facility Pre participation Screening Questionnaire *****only completed if necessary

Abbreviations: *BICAMS* Brief International Cognitive Assessment for MS, *SDMT* Symbol Digit Modalities Test, *CVLT* California Verbal Learning Test, *BVMT-R* Brief Visuospatial Memory Test-Revised, *WTAR* Wechsler Test of Adult Reading, *NART* National Adult Reading Test, *CMI* Cognitive-Motor Interference, *6MWT* Six Minute Walk Test, *IET* Incremental Exercise Test, *Functional MRI* Functional Magnetic Resonance Imaging, *GLTEQ* Godin Leisure-Time Exercise Questionnaire, *BDI-II* Beck Depression Inventory-II, *FAMS* Functional Assessment of Multiple Sclerosis, *EQ-5D-5L* European Quality of Life-5 Dimensions, *MSIS-29 V2* Multiple Sclerosis Impact Scale-29 Items Version2, *MSWS-12* Multiple Sclerosis Walking Scale 12 Items, *PDQ-20* Perceived Deficits Questionnaire 20 Items, *MFIS* Modified Fatigue Impact Scale, *HADS* Hospital Anxiety and Depression Scale

#### Neuropsychological evaluation

This is conducted in one session to document current levels of cognitive performance. The neuropsychological assessment includes a standard, widely accepted assessment battery for MS, the BICAMS [39]. The BICAMS consists of our primary outcome measure, the SDMT, as well as two other cognitive tests of verbal and visual learning and memory that will be used as secondary outcome measures, namely the California Verbal Learning Test (CVLT) and the Brief Visuospatial Memory Test (BVMT-R). The BICAMS is available in the languages represented within our study sample (English, Italian, French, Dutch and Danish). Language specific normative data are available in all cases [40–43] except in the case for Denmark, where the Dutch norm-data will be applied. Z-scores computed for inclusion criteria used regression-based norms adjusting for linear and non-linear age, sex and total years of education for either the raw or scaled scores from the respective normative data. To provide an assessment of cognitive reserve the Wechsler Test of Adult Reading (WTAR) [44] will be administered at baseline. The WTAR is validated in the participant’s primary language, and an estimated IQ will be computed based on performance. This estimated IQ score will serve as a common metric across all participants for inclusion in analyses. For those countries which do not have WTAR data, the comparable Adult National Reading Test (ANART) [45] will be used.

#### Physical performance

Height and weight will be used to calculate the Body Mass index (BMI). An incremental cardiopulmonary exercise test (CPET) will be conducted to assess peak aerobic capacity and power using the recumbent stepper that is also used for the exercise intervention. The incremental CPET will be undertaken in a standardized manner, and with scripted instructions to the participant. Expired gases will be collected using a 2-way non-rebreathable valve (e.g. Hans Rudolph, Kansas City, MO, USA or the like) and oxygen consumption will be continuously measured using an open circuit spirometry system (e.g. TrueOne, Parvo Medics, Sandy, UT, USA or similar). Participants will complete a 1-min warm-up at 15 W. The initial work rate will be set to 15 W and gradually increase until the participant reaches volitional fatigue. The work rate will be increased by 10 W per minute or 5 W per minute for participants with mild to moderate (i.e., EDSS of 4.0–5.5) or severe disability (i.e., EDSS of > 6.0), respectively. Participants will be encouraged to maintain a stepping rate of 60–100 steps per minute throughout the test depending on the work rate. Heart rate (Polar FT1 Heart Rate Monitor, Polar Electro Inc., Bethpage, NY, USA), and Ratings of Perceived Exertion (RPE) via the Borg Rating of Perceived Exertion Scale will be recorded every minute. The highest recorded 20-s rate of oxygen consumption value (VO2) will be recorded as peak oxygen consumption (VO2peak), expressed in mL/kg/min, optimally when two or more of the following criteria is satisfied: (1) respiratory exchange ratio (RER) of 1.10 or greater; (2) peak heart rate within 10 beats per minute of age-predicted maximum (i.e., 220-age); or (3) RPE of 17 or greater. The highest recorded power achieved during a 20-s period will be recorded as peak power output (Wpeak). This CPET protocol has previously been used in persons with MS [46], and will be used for measuring changes in aerobic capacity and for prescribing the recumbent stepper exercise training sessions [21].

Walking performance will be assessed by the 6 min walk test (6MWT). Subjects will be instructed to walk at their fastest speed, and to cover as much distance as possible, according to the script of Goldman et al. [47]. Subjects will be notified, without further encouragement, about each expired minute. Distances walked per minute and total distance will be recorded. Subjects walk back and forth along a 30-m hallway turning around cones at each end. In centers without this facility, a square trajectory is allowed given that this has been shown not to compromise results [48].

Cognitive-motor interference during walking will be quantified by a dual task cost (DTC) calculation in the motor and cognitive domains. The DTC calculation is based on a comparison of the performance on a single motor or cognitive task and the motor and cognitive performance during a concurrent motor plus cognitive dual task. The formula is DTC = ((DT-ST)/ST)*100. There are data suggesting that this dual modality testing can give additional insights into the putative benefits of the proposed interventions [49–51]. The single motor task requires the participant to walk at the fastest possible speed while maintaining safety for 60 s. The distance covered is measured. The setting for the 6MWT (30 m corridor) will be used for this test. The single cognitive task entails performing the alternating Latin alphabet for 60 s [52]. During the task, subjects list alternating letters of the alphabet as fast and accurately as possible (i.e., A, C, E, G, etc.). The number of correct letters provided by the subjects is recorded. The test requires working memory and inhibitory control. The cognitive-motor dual task involves walking at fast speed for 60 s with the alternating alphabet test as a concurrent task. Subjects will be instructed to divide attention equally on walking while correctly naming alternating letters of the alphabet.

Physical activity will be determined by accelerometry. Participants will wear the accelerometer (Actigraph; http://actigraphcorp.com/) on an elastic belt around the waist located above the non-dominant hip during the waking hours for 7 days before the first intervention week and during the week following completion of the intervention. This method has proven reliable in people with MS [53]. It will provide data on the degree of lifestyle physical activity (i.e. steps/day and minutes/day of moderate to vigorous physical activity) immediately before and after the intervention phase.

#### Patent reported outcomes (PRO’s)

PRO’s include the HADS, BDI-II, MFIS and PDQ. The MSWS-12, MSIS-29 version 2 and EQ-5D-5L are all standardized self-report outcome measures having strong reliability and validity in people with MS [54, 55] and with evidence supporting their responsiveness in rehabilitation trials [55–57]. Their wide use in MS interventional studies will enable comparisons between studies. The MSWS-12 provides information on the subjective impact of MS on walking and related activities and therefore adds important information regarding what can be obtained from objective measures of walking. Furthermore, it has strong psychometric properties [58]. The MSIS-29 is a disease specific measure of the impact of MS; it has a preference-based tariff [59] for use in sensitivity analyses for the Quality Adjusted Life Year (QALY) outcome, and has been endorsed for use in health economic analyses in MS studies [60]. This will complement the EQ-5D-5L, which is recommended for use in health policy decision making [60]. The FAMS was specifically developed for use with the MS population and has been shown to have adequate reliability and validity within this population. The measure contains 59 questions organized into 6 subscales: mobility, symptoms, emotional well-being, general contentment, thinking/fatigue, and family/social [61]. The thinking/fatigue subscale is composed of 9 items, including questions pertaining to task initiation, task completion, new learning, memory, concentration, and slowness of thought. Participants rate their symptoms on a 5-point Likert type scale. This assessment focuses on the person as a whole, investigating impairments, functional limitations, and disability in many areas of the person’s life. This overview of functional status at all levels is important in determining the impact of cognitive treatment on an individual’s everyday life**.** The FAMS has demonstrated good internal consistency, reliability and validity [61]. The scale has been used successfully to measure change from before to after cognitive rehabilitation [62]. To provide an assessment of anxiety and depression at each assessment, the Hospital Anxiety Depression Scale (HADS) [63] will be administered. The Modified Fatigue Impact Scale (MFIS) [64] will additionally be administered to assess fatigue at each assessment. Subjective cognitive deficits will be assessed with the Perceived Deficits Questionnaire (PDQ) [65].

#### Brain MRI protocol

Brain MRI scans will be obtained using 3.0 Tesla scanners. Budgetary constraints dictate that the MRI is obtained in one third of the sample (i.e. 120 subjects divided equally (*n* = 30) between the four treatment arms). The following sequences will be collected at baseline, termination of the interventions and after 24 weeks of follow up, following a standardized protocol of acquisition and careful guidelines for patients repositioning: axial T2 weighted Turbo Spin Echo (TSE); axial FLAIR; high resolution 3D sagittal T1-weighted sequence; axial DT sequence (55 contiguous, 2.5 mm thick, slices, #DW direction = 64) and T2*-weighted single-shot echo-planar imaging (EPI) during and active cognitive fMRI task and at rest.

For active fMRI, the Go/No-go task will be administered using a block-design, as previously described [66]. Reaction times, omission errors (no response although required), commission errors (false response without adequate cue), and the proportion of correct responses will be recorded using a response-box. Before imaging, participants will be familiarized with the paradigm. The fMRI Go/no-Go paradigm has been used both in cross-sectional [67] and longitudinal [68] studies of people with MS. Notably, a longitudinal (median follow up 20 months) neuropsychological and fMRI evaluation detected significant correlations between worsening of SDMT performances and modification of activation during the Go/no-Go task in several supra- and infratentorial brain regions [68]. Most importantly, the Go/no-Go task has already been validated for multicentric acquisition [66]. During resting state (RS) fMRI, subjects will be instructed to remain motionless, to close their eyes and not to think about anything in particular. Movements will be minimized using foam padding and ear blocks.

The total duration of MRI acquisition (structural plus functional MRI) will be approximately 50 min.

MRI analysis: MRI data acquired for the study will be analyzed centrally at one Neuroimaging Research Unit (Hospital San Raffaele, Milan, Italy).

Lesion and atrophy analysis: Brain T2-hyperintense and T1-hypointense lesion volumes (LV) will be measured on FLAIR and 3D T1-weighted scans, respectively, using a local thresholding segmentation technique (Jim 7.0, Xinapse Systems, West Bergholt, UK). New lesions at follow-up will be counted. Normalized brain (NBV), WM (WMV) and GM (GMV) volumes will be measured on 3D T1-weighted scans using the SIENAx software, after T1-hypointense lesion refilling.^168^ Hippocampal volume will be estimated using FIRST software.

Mapping changes in gray matter (GM) and white matter (WM) structures: Voxel-based Morphometry (VBM) with DARTEL method will be applied to determine between-group differences of GM volumes at baseline, using SPM12 and 3D T1-weighted images. Tensor-based Morphometry (TBM) [69] will be applied to map the longitudinal regional variations of GM volume at the different time points.

Diffusion-weighted images will be corrected for distortions induced by the eddy currents and for head movements, and transformed to MNI (Montreal Neurological Institute) space. Then, using the FMRIB’s Diffusion Toolbox (http://www.fmrib.ox.ac.uk), the DT will be estimated in each voxel by linear regression [70] and mean diffusivity (MD), radial diffusivity (RD), axial diffusivity (AD) and fractional anisotropy (FA) maps derived. Tract-based Spatial Statistics (TBSS) will be used to define the patterns of microstructural WM abnormalities on diffusion tensor images at baseline and their variations during the follow up.

Analysis of fMRI data: Active and RS fMRI data will be pre-processed using SPM12. Activations during the Go/no-Go task will be estimated using SPM12. An independent Component Analysis (ICA) will be used to decompose RS fMRI data into spatially independent maps and time courses, using the GIFT software [71]. Individual functional maps will be converted to Z-scores before entering group statistics, to obtain voxel values comparable across subjects. A systematic process will be applied to inspect and select the components of interest from the estimated ones. The association of each component spatial map with a priori probabilistic maps of GM, WM, and CSF within the MNI space will contributed to identifying the components with a signal change correlated to the GM. Components with a high correlation with cerebrospinal fluid or WM, or with a low correlation with the GM, will be excluded. In addition, to identify components with potentially functional relevance, a frequency analysis of IC time courses will be performed to detect those with a high (50% or greater) spectral power at a low frequency (between 0.01 and 0.05 Hz) [72]. The spatial patterns of the remaining ICs will be sorted out on the basis of their matching with relevant RSNs found in previous studies [73–76] A seed-base RS functional connectivity (RS FC) analysis, using the thalami as a seed, will also be performed to assess modifications of RS FC of the thalamic network in the main study groups and their correlations with clinical scales [77].

#### Standardisation and data quality

To promote data quality, all assessment activites are manualised. Further, before initiating recruitment all PI’s, blinded and unblinded assessors participated in a training session at which all of the tests were discussed and demonstrated. Following this, every site performed a rehearsal incremental CPET on at least one MS patient and sent the data to the responsible PI for review. To ensure that all sites initialise their accelerometers correctly, the assessors themselves wore a device for 7 days, and the data sent to the same PI for review. Similarly, a mock MRI scan will occur at the four centers participating in the MRI substudy. All data will be entered into REDCap [78]. Before entering any data in the actual study database, all assessors will undertake practice lessons and complete a practice certification consisting of a set of ficticious data. Data will be downloaded regularly for quality control purposes and basic reports will be generated via the REDCap system and SAS. Data forms will employ validation and skip pattern logic that provides constrained input whenever possible. Errors or questionable data will be turned into data queries and will be sent by the Data Coordinating Center to the sites for correction and/or clarification. Reports will be produced and include information on data quality, completeness and protocol adherence.

Confidentiality is guaranteed through anonymity. Each participant is given an unique case number, and the Data Coordinating Center at Washington University are not given any identifying data.

#### Power analysis

The primary outcome measure is the SDMT. A four-point improvement on the SDMT is considered clinically useful [37, 38]. Evidence for the reliability of the test was initially obtained in a study of 80 adults administered the test in 2 test sessions approximately 30 days [79]. Comparisons of test scores obtained at times 1 and 2 resulted in a test-retest correlation of 0.80. Individuals tested at baseline obtained a score of 56.79 ± 9.84. Scores increased an average of 3.67 points to 60.46 ± 11.16 at retesting. Such an increase in scores at the second test reflects a “practice effect,” which is commonly seen in test-retest situations [80]. This level of test-retest correlation has been reproduced multiple times and is often higher. We expect a learning curve to be present in all groups and this will in effect wash out in the analyses as our comparisons will utilize comparative changes in means.

Camp et.al. in a primary progressive population studied longitudinally revealed standard deviations of 13.96 at baseline, 15.24 at 1 year and 14.32 at 2 years [81]. Sonder et.al. showed a standard deviation of 14.3. Further, the change over time was generally impacted slightly by the learning curve returning to baseline as the time scale extended [82]. Thus, we can think of changes from baseline to 12 weeks or 6 months in the present study as potentially representing a zero change except for the intervention effect.

The reliability of the SDMT is high, 0.80 or higher as noted above, implying that the correlation between two measures that are not materially changing have high reliability and thus the standard deviation of the change should be relatively small. If we assume that the correlation between two measures is only 0.50, then our estimated standard deviation of the change would be the same as the cross-sectional value (i.e. 10 to 16). However, given the high test-retest correlation, we should assume the correlation between the measures is higher. Assuming it is 0.80, then the estimated standard deviation would be between 6.3 and 10.1 (assuming the cross-sectional standard deviation is 10 or 16 respectively). Thus assuming a standard deviation of the changes of 7 to 8, seems reasonable and 8 may be slightly high, since 16 is at the upper end of most reports. If the standard deviation is 12 cross-sectionally, then the estimated change standard deviation is 7.6. Nevertheless, for sample size estimation it is better to be a bit conservative.

We propose to treat four groups of participants as noted above. We estimated our sample size using a standard 1-factor analysis of variance approach with a Type I error set at 5%. We computed the sample size necessary to achieve 80% power for such a design assuming conservative changes. For simplicity we used 4 points for the combined treatments, *assuming* that we want to demonstrate a clinically meaningful difference on average and that the two interventions are additive; 4 more correct answers has been suggested by the FDA as a meaningful change [37]*.* We also assumed a change of 2 answers for each of the single interventions and 0 for the sham group [83]. (Note *again* that the learning curve and practice effects will contribute equally to each group and the results shown below are the same if we had chosen 6, 4, 4, 2 *or* other combinations with the same relative spread to accommodate the practice effects, etc.)

Table 6 shows that with 90 participants per treatment group at the time of analysis, there is over 80% power to detect differences as specified (4,2,2,0) across the four groups when the standard deviation of the change is 8 points and the overall Type I error to detect any mean differences is 0.05.

**Table 6 Tab6:** Power for 4 group Analysis of Variance with mean changes in the SDMT of 4 more correct for the combined group; 2 more correct for each of the single intervention groups and 0 change for the Sham Group

**Power**	**n**	**Total N**
0.52751	50.00	200
0.57247	55.00	220
0.61476	60.00	240
0.65423	65.00	260
0.69081	70.00	280
0.72449	75.00	300
0.75533	80.00	320
0.78341	85.00	340
0.80885	90.00	360
0.83179	95.00	380
0.85239	100.00	400

In order to assess the sensitivity of these calculations to assumptions, we conducted a few additional patterns of response and standard deviations. Clearly for any standard deviation smaller than 8, we have more power. For example, if the standard deviation of the change were 7 instead of 8, the power is 91% with 90 patients per group and 81% with 70 per treatment group. If the treatment difference pattern is 4,1,1,0; the power is 86% with four groups assuming a standard deviation of 8.

If the change is less in the combined treatment group, and the pattern is say 3,2,1,0 and a standard deviation of the change is 8, the power is 59%. If the pattern is 3,2,1,0 and the standard deviation of the change is 7, then the power is 71%. Thus, the power is reasonably high for a variety of the patterns. Obviously increasing the sample size in each treatment group increases the power, but we will increase the number recruited and randomized to account for potential dropouts, thus should have ample power under these assumptions.

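### An SD of change of 8 is presented as cautious, but at the plan's own correlation of 0.80 the progressive-MS SDs it cites give about 8.8 to 9.6, and omnibus power of about 63 to 72% rather than 81%

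*Protocol article*

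**What the plan says.** All of this is in the protocol article, section Power analysis.

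- **Cited spread.** A longitudinal study of a primary progressive population "revealed standard deviations of 13.96 at baseline, 15.24 at 1 year and 14.32 at 2 years". A second study is cited with an SD of 14.3; the text does not state its population. A reliability study of 80 adults, retested after about 30 days, gave SDs of 9.84 and 11.16 and a correlation of 0.80.
- **Conversion to an SD of change.** "Assuming it is 0.80, then the estimated standard deviation would be between 6.3 and 10.1", for cross-sectional SDs of 10 and 16. A further worked value, 12 giving 7.6, has no source attached.
- **Choice.** "Thus assuming a standard deviation of the changes of 7 to 8, seems reasonable and 8 may be slightly high". The reason given is that 16 lies at the top of what most reports show. The paragraph closes by favouring some conservatism in sample size estimation.
- **Result.** For 90 per arm analysed, the claim is that "there is over 80% power to detect differences as specified (4,2,2,0) across the four groups". The SD behind this claim is 8, and Table 6 prints 0.80885.
- **Sensitivity.** Other mean patterns are tried with an SD of 8 or 7. No power figure uses an SD above 8.

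**The concern.** The section cites SDMT spread in a progressive population and gives a rule for turning spread into an SD of change, but it never puts the one through the other. The SD it adopts is lower than any that this step would produce at the correlation it uses. The reason offered does not support the adopted value either: the section itself maps 16 to 10.1, so placing 16 at the upper end says little about whether 8 is high.

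This matters because the total of 360 is justified by one line of Table 6. A reader told that 8 errs on the safe side will take 81% as a floor. The sensitivity paragraph reinforces that impression by moving the SD only downward, although the section's own range extends to 10.1.

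**Working it through.** **Inputs** (all from Power analysis): four equal arms, 90 per arm at analysis, mean changes 4, 2, 2, 0, two-sided framework with omnibus alpha 0.05, SD of change 8, r = 0.80, and the cited cross-sectional SDs.

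**Step 1: reproduce the stated power.** One-way ANOVA, noncentral F with 3 and 4 × 90 − 4 = 356 degrees of freedom. The arm means average 2, so the sum of squared deviations is 4 + 0 + 0 + 4 = 8. The noncentrality is 90 × 8 / 8² = 11.25, and the power is 0.80885. This matches Table 6, as do its other ten rows. The secondary figures (SD 7, and the patterns 4,1,1,0 and 3,2,1,0) reproduce to within one percentage point.

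**Step 2: reproduce the conversion rule.** SD of change = SD × √(2(1 − r)). At r = 0.80 the factor is √0.4 = 0.632, which gives 6.3 for 10, 7.6 for 12 and 10.1 for 16, as printed.

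**Step 3: apply the rule to the cited SDs, r = 0.80, 90 per arm.**

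| Cross-sectional SD | SD of change | Power |
|---|---|---|
| 13.96 (primary progressive, baseline) | 8.83 | 71.8% |
| 14.3 (population not stated) | 9.04 | 69.5% |
| 14.32 (primary progressive, 2 years) | 9.06 | 69.4% |
| 15.24 (primary progressive, 1 year) | 9.64 | 63.3% |

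**Step 4: use the SDs of two different visits.** SD of change = √(a² + b² − 2rab), with r = 0.80.

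| Visit pair | SD of change | Power |
|---|---|---|
| 13.96 and 14.32 | 8.95 | 70.5% |
| 13.96 and 15.24 | 9.31 | 66.7% |
| 15.24 and 14.32 | 9.39 | 65.9% |

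**Step 5: work back from 8.** At r = 0.80, an SD of change of 8 needs a cross-sectional SD of 8 / 0.632 = 12.65. That is below every primary-progressive SD cited.

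**Step 6: find the correlation that SD 8 implies.** r = 1 − 8² / (2 × SD²). This is 0.836 for 13.96, 0.844 for 14.32 and 0.862 for 15.24.

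**Step 7: power if r is higher (assumed values).**

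| r | SD 13.96 | SD 14.32 | SD 15.24 |
|---|---|---|---|
| 0.80 | 72% | 69% | 63% |
| 0.84 | 82% | 80% | 74% |
| 0.85 | 85% | 83% | 77% |
| 0.86 | 87% | 85% | 80% |
| 0.90 | 96% | 95% | 92% |

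**The case against.** The strongest reply is that 0.80 is a floor. The section puts reliability at 0.80 or above and says that later studies often find more. A shift of 0.04 to 0.06 restores about 80% power. This stands, and it is why the lower power can only be stated conditionally. It does not rescue the description of 8 as cautious: the section gives no figure above 0.80, makes no calculation with one, and takes its 0.80 from retest at about 30 days when the trial interval is 12 weeks.

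Second, the study of 80 adults is the only cited source that reports both visit SDs and a correlation. It implies √(9.84² + 11.16² − 1.6 × 9.84 × 11.16) = 6.76 and power of 93%. Correlation depends on spread. If that SD of change carried over to the progressive cohort, r there would be about 0.88 to 0.90 and 8 would indeed be cautious. That is possible, but it is an assumption the section does not make, and the text does not describe those adults as having MS.

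Third, the 63% end uses the 1-year SD of 15.24 at both visits. This also stands; the visit pairs give 66 to 71%.

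Fourth, the SDMT entry threshold may narrow the baseline spread. The section does not argue this, and a narrower range could also lower the correlation. Under a linear model with r = 0.80, the SD given baseline is still √(1 − 0.64) = 0.6 times the cross-sectional SD. That is 8.4 for 13.96 and 9.1 for 15.24, with power of 77% and 68%.

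**Conclusion.** The point holds in conditional form. At the one high correlation the plan calculates with, its cited primary-progressive SDs give an SD of change of about 8.8 to 9.6. Calling 8 a little high therefore contradicts the plan's own figures. If r is 0.80, omnibus power at 90 per arm for 4, 2, 2, 0 is about 63 to 72% (66 to 71% with visit pairs), which is 9 to 18 points below the stated 81%. If r is about 0.84 to 0.86 or higher, the 81% is broadly right. These figures rest on the plan's means, on 90 per arm at analysis, and on the cited SDs applying to the enrolled population.

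A reader might infer three stronger things that the documents do not support:

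- **That Table 6 is wrong.** It is not; every row reproduces.
- **That the trial's true power is 63 to 72%.** This would require r to be exactly 0.80, and the text allows more.
- **That 360 is too few and must be raised.** The true correlation is not known from this document, so that does not follow.

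What is at fault is the choice and description of one input, and a sensitivity analysis that looks only in the favourable direction.

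**What to change.** In Power analysis:

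1. Remove the statement that 8 may be on the high side, and the suggestion that the choice is conservative.
2. State that an SD of change of 8 assumes a correlation of about 0.84 to 0.86 at the cited primary-progressive SDs. Otherwise, keep 0.80 and state the power as about 63 to 72%.
3. Next to the SD 7 sensitivity, add rows at 90 per arm for SD 8.8 (72%), 9.0 (70%) and 9.6 (64%).
4. Optionally, compute a blinded pooled SD of 12-week SDMT change. The Study status section reports 90 participants past the immediate follow-up by March 2020. Pooling without arm labels adds little: under 4, 2, 2, 0 the between-arm variance is 8 / 4 = 2, so an SD of 8 would appear as √66 = 8.1. With 90 participants the standard error of an SD near 8 is about 8 / √(2 × 89) = 0.6. The check would therefore be informative but would not separate 8 from 8.8 sharply.

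The cost is a few sentences, three table rows and, if wanted, one blinded run. No patients are added and no test changes. The drawback is a less favourable stated power.
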